#### 10.1.1 Imputation of App-recorded data

The daily questionnaire taken via the DizzyQuest app is likely to contain missing data. All other missing data will be labelled 'NAmissing' in SPSS. Multiple imputation will be used to create complete data sets. Depending on the missing data pattern different strategies will be followed.

Imputation variables are base line measurements, time-course measurements and daily App-data.

- Missingness  $\leq 10\%$

If little data is missing, the data will be treated as one data-row per patient (wide format).

In this case, information for imputing missing values will be taken from the exact same time points of other patients. This strategy can account for possible time trends.

- Missingness  $> 10\%, \leq 50\%$

If more data is missing, the data of each patient will be split into one row per day (long format), when the previous 10 days will be included in each row. After imputation, the previous days will be removed to avoid duplication of data. This strategy includes information on missing data across time periods and can lead to wrong imputations for time trends longer than 10 days.

- Missingness  $> 50\%$

The same strategy as for missingness between 10% and 50% is followed except for including a smaller time window. 10 previous days will be used. If all primary outcome data are not available (missing), the participant will be excluded from the analyses. The a priori sample size estimation has been corrected for this.

The above cut-offs and time ranges reflect expectations. Actual values will be selected based on the variability of imputed values.

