#### **10.1.2 Computation of outcome**

The outcome will be determined from the imputed App-data. It is expected that attacks are reported reliably and missing data can be reliably imputed as being attack free. In principle, a patient can be sometimes imputed as having an attack on otherwise as being attack-free. To account for these potential cases, a cut-off of 10% for the attack probability (as the imputed frequency for having an attack) will be used to determine presence/absence of attacks.

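### The settings that impute the primary outcome are left to be chosen from the imputed values themselves, with no rule, timing or blinding, and the tier above 50% missingness contradicts its own window

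*Protocol*

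**What the plan says.** Protocol section 10.1.1 sorts the app data into three tiers of missingness.

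- **Up to 10%:** one row per patient. Missing values are informed by other patients at the same time points, so no look-back window applies.
- **Above 10% and up to 50%:** one row per day, "when the previous 10 days will be included in each row".
- **Above 50%:** the same strategy, "except for including a smaller time window. 10 previous days will be used".

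The section ends by making all of this provisional. It describes the cut-offs and windows as expectations only, and continues: "Actual values will be selected based on the variability of imputed values".

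Section 10.1.2 then states: "The outcome will be determined from the imputed App-data". A patient who is imputed sometimes with and sometimes without an attack is classified by a threshold: "a cut-off of 10% for the attack probability (as the imputed frequency for having an attack) will be used". The section expects that "missing data can be reliably imputed as being attack free".

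Section 10.1 tests the number of attack-free patients at 12 months by chi-square or Fisher's exact test, two-sided at 5%. Section 4.4 adds two sensitivity analyses, in which missing outcomes count as failures or as successes.

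**The concern.** The settings that generate the endpoint are to be chosen by looking at the values from which the endpoint is computed. The protocol does not say how much variability is acceptable, which direction is preferred, who chooses, when, or whether the chooser is blind to allocation. That is uncontrolled analyst freedom inside the derivation of the only primary outcome.

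This is not a detail left to a statistical analysis plan. The protocol prescribes a data-driven choice, and a plan that fixed the values in advance would conflict with it.

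The second defect is separate. An analyst with more than 50% missing days cannot follow both halves of the instruction and must invent a window.

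At stake is whether the count of attack-free patients can be reproduced from the protocol, and whether a reader can be sure that the settings were not chosen with the result in view.

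**Working it through.** **1. The two windows side by side (10.1.1).** The tier from 10% to 50% uses 10 previous days. The tier above 50% is described as using fewer and then states 10. Ten is not smaller than ten, so the text contradicts its own figure.

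**2. Do the settings reach the endpoint?** Yes, in sequence. The cut-off decides whether a missing day is informed by other patients on the same day or by lagged days, and in the lagged tiers the window decides how many. Together these shape the imputed attack probability. Section 10.1.2 turns that probability into success or failure at 10%.

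An illustration of how sharp this step is, with assumptions that are not in the protocol: a constant daily imputed attack probability q, independent days, no recorded attack, and the 10% threshold read as the chance of any imputed attack over k missing days.

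P(any imputed attack) = 1 − (1 − q)^k

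- q = 0.001, k = 30: 1 − 0.999^30 = 3.0%, classed attack free
- q = 0.005, k = 30: 1 − 0.995^30 = 14.0%, classed not attack free
- Missing days needed to pass 10%: 106 for q = 0.001, 53 for 0.002, 22 for 0.005 and 11 for 0.01

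If two settings gave daily probabilities this far apart, they would classify the same patient differently. The protocol does not say whether they would.

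**3. How many reclassified patients would matter?** Inputs from section 4.4: 95% v 70% attack free and 37 per arm. The nearest whole numbers are 0.95 × 37 = 35.15, so 35, and 0.70 × 37 = 25.9, so 26. Fisher p-values are two-sided. Chi-square is uncorrected, with z = (a − b)/37 ÷ √[p(1 − p) × 2/37] and p = (a + b)/74.

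| EDB v decompression | Patients reclassified | Fisher p | Chi-square p |
|---|---|---|---|
| 35/37 v 26/37 | 0 | 0.012 | 0.006 |
| 34/37 v 26/37 | 1 | 0.035 | 0.018 |
| 34/37 v 27/37 | 2 | 0.064 | 0.033 |
| 33/37 v 26/37 | 2 | 0.081 | 0.043 |
| 35/37 v 28/37 | 2 | 0.046 | 0.022 |
| 35/37 v 29/37 | 3 | 0.085 | 0.041 |

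Worked case, 34/37 v 27/37: p = 61/74 = 0.8243; z = (7/37)/√(0.8243 × 0.1757 × 2/37) = 0.1892/0.0885 = 2.14; chi-square p = 0.033.

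From the planned result, one reclassified patient does not change the conclusion under either test in the case shown. Two can change it under Fisher, depending on which two. None of these tables crosses 0.05 under chi-square.

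**The case against.** Several points on the other side are sound.

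- **Selection is on variability, not on the treatment contrast.** A reader might infer that the sentence lets the analyst favour EDB, or that the least variable setting wins. The text says neither, and selecting on variability does not by itself favour an arm.
- **Much of the sensitivity comes from the 10% probability threshold.** That threshold stands in 10.1.2, after the sentence that makes the settings provisional, and is not itself declared provisional.
- **The range of settings is narrow as written.** Under the stated cut-offs no window exists up to 10% missingness, and the protocol names no window longer than 10 days. The imputation also draws on baseline and time-course measurements. A simulation that varies the window over several weeks, or imputes from recent attacks alone, would overstate the effect of this plan.
- **There are mitigations.** Section 12.1 has nightly status emails and contact with participants who miss questionnaires. The failure and success analyses of 4.4 partly bound the dependence. Section 10.1.2 expects missing days to impute as attack free.
- **An SAP, not seen here, may lock the settings.**

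These points limit the size of the problem but do not remove it. The sensitivity analyses do not fix the primary derivation, an expectation is not a rule, and the sentence still directs a choice from the imputed data. The contradiction over the window is untouched.

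**Conclusion.** Two defects stand on the text alone: a primary-endpoint derivation left open to a post-hoc choice without criterion, timing or blinding, and a tier above 50% whose stated window contradicts its description.

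The size is conditional. Two reclassified patients of 74 can move the planned result from Fisher p = 0.012 to 0.064 or 0.081, while chi-square stays at 0.033 and 0.043. This assumes that the observed result lies near the planned one and that a change of setting would move those particular patients. Both depend on the amount of missing app data. The protocol calls missing data likely but gives no expected rate.

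A reader might infer that the trial's conclusion does depend on the chosen setting. The documents do not show this. Nor do they support a general claim that one patient decides significance: 30/32 v 24/32 against 30/32 v 25/32 crosses 0.05 under chi-square (0.039 and 0.072) but not under Fisher (0.082 and 0.148), the test on which section 4.4 sizes the trial.

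**What to change.** 1. Delete the sentence in 10.1.1 that lets the values be selected from the variability of the imputed values.
2. Fix the cut-offs and windows in advance. Alternatively, choose them by a stated rule on data pooled over arms and blind to allocation. In either case, lock them before the outcome is computed and before unblinding.
3. If data are needed to choose, the diary kept from inclusion to surgery (section 8.3.1) is one possible source. It has a limit: section 4.2 selects patients with active attacks, so a setting tuned there may not suit postoperative data that are mostly attack free.
4. Give the tier above 50% its own smaller window, or merge it with the tier from 10% to 50%.
5. Report one or two alternative windows as labelled sensitivity analyses, beside the failure and success analyses of section 4.4.

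The cost is protocol or SAP wording and a little programming. No patients or visits are added.

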#### **10.1.2 Computation of outcome**

The outcome will be determined from the imputed App-data. It is expected that attacks are reported reliably and missing data can be reliably imputed as being attack free. In principle, a patient can be sometimes imputed as having an attack on otherwise as being attack-free. To account for these potential cases, a cut-off of 10% for the attack probability (as the imputed frequency for having an attack) will be used to determine presence/absence of attacks.

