#### 4.4 Sample size calculation

The sample size for this RCT was computed using software package PASS 11. The sample size calculation is based on the study performed by Saliba (Saliba 2015), in which complete control of vertigo was reached in 96,5% of the patients who underwent EDB. According to literature, endolymphatic sac decompression is effective in  $\pm 70\%$  of the patients (Brinson 2007, Convert 2006, Durland 2006).

We compare MD participants undergoing an operation with clip (EDB group: A group) independently with MD participants undergoing operation without clip (decompression group: B group). Null hypothesis is that the percentage points difference between groups is nil ( $p_A = p_B$ ), with two-sided alternative hypothesis ( $p_A \neq p_B$ ) and with anticipated 25% percent difference ( $p_A = 95\%$  and  $p_B = 70\%$ ). Power is at least 80%. The chance of a false positive finding for either of the analyses is controlled at the 5% level (family wise error rate). To obtain a power of at least 80% for Fisher's Exact test, the required sample size is 32 in groups A and B (allocation ratio = 1). Loss to follow-up will likely occur in a small percentage of cases ( $n=5$  per arm). No selective loss to follow-up is anticipated and a missing-at-random assumption seems reasonable. Missing outcomes will therefore be imputed using multiple imputation in the main analysis. Two sensitivity analyses will be conducted as well, where missing outcomes will be treated as failures or success, respectively. In this case the sample size would be 37 in group A and B (allocation ratio = 1). The total number of participants would be 74.

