## 8. METHODS

### 8.1 Study parameters/endpoints

#### 8.1.1 Main study parameter

The main study parameter is the number of patients free of vertigo attacks at 12 months after surgery. This parameter was chosen because vertigo is the most invalidating symptom of MD.

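### The 10% cut-off in 10.1.2 replaces pooling of the imputed app data, and with no assessment window stated, missing diary days can decide the primary outcome

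*Protocol*

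**What the plan says.** - **Endpoint.** Protocol 8.1.1: "The main study parameter is the number of patients free of vertigo attacks at 12 months after surgery". Section 10.1 defines the outcome in the same terms. Neither gives the days or months over which freedom from attacks is judged.
- **Imputation.** Section 4.4: "Missing outcomes will therefore be imputed using multiple imputation in the main analysis". Section 10.1.1 uses multiple imputation for the daily app data, in three tiers by amount of missingness.
- **Reduction to one value.** Section 10.1.2 expects that "missing data can be reliably imputed as being attack free". It allows that a patient may be imputed with an attack in some data sets and without one in others, and resolves this as follows: "a cut-off of 10% for the attack probability (as the imputed frequency for having an attack) will be used to determine presence/absence of attacks". Section 10.1 applies one chi-square or Fisher's exact test to the number of attack-free patients. No pooling step is described.
- **Wholly missing outcome.** Section 10.1.1: "If all primary outcome data are not available (missing), the participant will be excluded from the analyses". Section 10 labels all analyses intention to treat.
- **Tier for more than 50% missing.** It follows the middle tier "except for including a smaller time window. 10 previous days will be used"; the middle tier also uses the previous 10 days.
- **Settings.** On the tier cut-offs and time ranges, 10.1.1 says: "Actual values will be selected based on the variability of imputed values".

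**The concern.** Multiple imputation carries the uncertainty about missing days into the comparison between arms. A threshold applied before the test removes it: an imputed attack chance of 11% becomes a certain failure and 9% a certain success. For a participant with no recorded attack, the imputed chance rises with the number of missing days, and that number rises with the window length. The window is not stated. This classification feeds the only primary endpoint, so the success proportions, the contrast between arms and the power all depend on it. The contradictory instructions for wholly missing outcomes, and settings that may be chosen once imputed values are visible, leave more of the primary analysis open after data collection.

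**Working it through.** The protocol gives no derivation for the 10%, so there is no figure to reproduce. The check asks how the rule behaves.

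**Inputs from the protocol.** 10% cut-off (10.1.2); anticipated success 95% vs 70% and 37 per arm (4.4); missingness foreseen from under 10% to over 50% (10.1.1).

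**Assumptions, because the protocol gives no values.** Days are missing independently at random. The imputed attack probability q per missing day is constant. A month has 30.4 days. The 10% applies to the patient over the window.

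**Step 1: missing days needed to become a failure.** With no recorded attack and m missing days, the imputed chance of at least one attack is P = 1 - (1 - q)^m. The smallest m with P > 10%:

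| Imputed attacks per month | q per day | m | P at m |
|---|---|---|---|
| 0.1 | 0.33% | 32 | 10.0% |
| 0.25 | 0.82% | 13 | 10.2% |
| 0.5 | 1.64% | 7 | 11.0% |
| 1 | 3.29% | 4 | 12.5% |

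**Step 2: effect of the unstated window.** With q = 0.5/30.4 and 10% of days missing:

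- 30 days: m = 3, P = 4.9%, attack free
- 60 days: m = 6, P = 9.5%, attack free
- 183 days: m = 18.3, P = 26%, failure
- 365 days: m = 36.5, P = 45%, failure

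The same diary behaviour changes class with the window alone.

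**Step 3: a pooled daily rate.** Suppose every patient is imputed at the overall rate. Average failure is (5% + 30%)/2 = 17.5%. At 1 attack per month among failures, q = 0.175/30.4 = 0.576% per day. Then 18 missing days give P = 9.9% and 19 give 10.4%. Over 183 days with 10% missing, the expected number of missing days is 18.3, so close to half of the truly attack-free participants cross the line.

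**Step 4: simulated trials**, 37 per arm, true rates 95% vs 70%, failures having 1 attack per month, two-sided Fisher test. Ranges are across repeated runs.

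| Imputation model | Window, days missing | Classed attack free | Power (true outcomes) |
|---|---|---|---|
| Pooled rate | 183 days, 10% | 51-54% vs 40-41% | 20-24% (about 76%) |
| Pooled rate | 365 days, 10% | about 3% vs 3% | below 1% (about 78%) |
| Pooled rate | 30 days, 5% | 95.0% vs 71.4% (true 94.8% vs 70.4%) | 73% (75%) |
| Own rate, shrunk to the pooled rate with a weight of 10 days | 183 days, 10% | 95% vs 70% | 77-79% (about 77%) |

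**Step 5: type I error.** With 82.5% success in both arms, Fisher rejection never exceeded 3.5%. The uncorrected chi-square test stayed within simulation noise of 5% (at most 6.6%).

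**Step 6: number of imputations.** With 5 imputations, one imputed attack is 1/5 = 20%, so a single hit makes a failure. With 10, one hit is exactly 10%, and the text does not say on which side that falls.

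**Step 7: texts side by side.** Section 4.4 imputes a missing outcome in the main analysis; 10.1.1 removes a participant whose primary data are all missing. Both cannot govern, and removal does not fit the intention-to-treat label. The tier above 50% announces a shorter window but repeats 10 days.

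**The case against.** The strongest reply is that the large figures come from the assumed imputation model, not from the cut-off itself. Section 10.1.1 lists daily app data among the imputation variables, and one row per patient lets a patient's other days act as predictors. The statement that "information for imputing missing values will be taken from the exact same time points of other patients" might lead a reader to infer that the lowest tier ignores the patient's own history; the text does not establish that. With an own-rate model the rule did almost no harm. This stands, and it limits the size but does not remove the point: the protocol does not fix the model, and the cut-off still stands in place of pooling.

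Further points, and what remains of them:

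- **Standard error.** A reader might infer that testing collapsed imputations makes the standard error too small and inflates false positives. Nothing in the protocol shows this, and the null simulations do not either.
- **Per-day reading.** If the 10% applied to each day, q would be 0.3% to 6.6% at 0.1 to 2 attacks per month, so at those rates every missing day would count as attack free. The sentence before the cut-off speaks of a patient, so this reading is secondary.
- **Pre-operative rates.** Using the eligibility minimum as the imputed rate would put failure at 5 missing days. It does not carry over to post-operative patients, of whom 70% to 95% are expected to be attack free.
- **Retuning.** The freedom to choose values covers the tier cut-offs and time ranges of 10.1.1, not expressly the 10%.
- **Safeguards.** Attacks have their own short questionnaire (8.3.1), missed questionnaires are followed up (12.1), and a recorded attack inside the window settles the outcome. These may reduce gaps but leave the rule unchanged. The failure and success sensitivity analyses in 4.4 are not extended to partly missing diaries.
- **Left to an analysis plan.** Pooling detail often is. Here the protocol itself states a different rule.

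**Conclusion.** The point holds. Section 10.1.2 substitutes a threshold for pooling, contrary to the multiple imputation announced in 4.4 and 10.1.1, and the endpoint has no window. Participants with no recorded attack and some missing days can be classed by their gaps. The size ranges from negligible (own-rate model, or 30 days with 5% missing) to severe (pooled rate over 183 days or longer with 10% missing). It rests on assumed attack rates, random missingness and an assumed imputation model, so no single figure can be claimed for this trial. The demonstrated harm is misclassification and loss of contrast, not excess false positives. The impute-or-exclude conflict and the repeated 10 days are plain contradictions in the text. The freedom to set tiers after seeing imputed values is a further weakness. Because all of this defines the primary outcome, it should be settled before unblinding.

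**What to change.** 1. State one assessment window ending at 12 months in 8.1.1 and 10.1. Its length is for the investigators to choose.
2. Derive attack-free status over that window within each imputed data set, estimate the between-arm comparison in each, and pool with Rubin's rules. Name that pooled comparison in 10.1. A stratified estimator is optional; this point does not require it.
3. Delete the 10% cut-off and the expectation that missing days can be taken as attack free.
4. Include the patient's own attack history and treatment arm in the imputation model at every level of missingness.
5. Delete the exclusion sentence in 10.1.1 so that 4.4 governs.
6. Correct the window in the tier above 50%.
7. Lock all imputation settings before unblinding.
8. Extend the failure and success sensitivity analyses of 4.4 to partly missing diaries.

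The cost is rewording of 8.1.1, 10.1, 10.1.1 and 10.1.2, some programming, and possibly wider intervals. No new data are needed.

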### **10.2 Secondary study parameters**

The Patient Reported Outcome Measures (PROMs) used in this study are assumed to be continuous numerical and will be tested checked for near-Gaussian distribution normality before analysis. Results will be described as means (with 95%CI) in case of near-Gaussian distribution or, otherwise medians (with IQR) will be presented at each time point.

Categorical outcomes will be presented in numbers of participants with accompanying percentages of group total.

#### **10.2.1 Missing data**

For the missing data in the various questionnaires, we use the standard rules concerning missing data.

#### **10.2.2 Computation of outcome**

All secondary outcomes will be analysed using a linear mixed model (EDB vs decompression group) at the different time measurement point.

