| Ménière's disease      | First attack                                          | dd-mm-yyyy                                     |
|                        | Duration of MD                                        | Days (calculated)                              |
|                        | Most recent attack                                    | dd-mm-yyyy                                     |
|                        | Mean number of attacks per month in the last 6 months | Number                                         |
|                        | Previous treatments                                   | None
Betahistine
Intratympanic injection |
|                        | Number of sessions IT injections                      | Number                                         |
|                        | Number of IT injections                               | Number                                         |
|                        | Substrate of IT injections                            | Dexamethason
Kenacort
Solumedrol         |
| Comorbidities          | All                                                   | (Free text)                                    |
| In-/exclusion criteria | Meets in- and exclusion criteria                      | Yes/no                                         |
| Attacks                | Number of attacks in the past 6 months                | Number                                         |
|                        | Number of attacks in the past 2 months                | Number                                         |
| Informed consent       | Informed consent obtained?                            | Yes/no                                         |
|                        | Date of informed consent                              | dd-mm-yyy                                      |
|                        | Version of IC-form                                    | Free text                                      |

| Physical examination | vHIT                  | Gain left/right                                                  |
|----------------------|-----------------------|------------------------------------------------------------------|
|                      | Weber                 | No lateralization
Lateralizes to left
Lateralizes to right |
|                      | Rinne right           | Positive
Negative                                             |

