|                      | Rinne left            | Positive
Negative                                             |
|                      | Dix Hallpike          | Positive
Negative                                             |
|                      | If positive: side:    | Left
Right                                                    |
|                      | Diadochokinesis       | Normal
Abnormal                                               |
|                      | If abnormal: side     | Left
Right                                                    |
|                      | Eye pursuit movements | Smooth
Abnormal                                               |
|                      | If abnormal: direct   | Left
Right
Up
Down                                      |

An MRI- and CT-scan will be performed and the patient is referred to a vestibular therapist. A PTA, vHIT and calorigram will be performed. Moreover, from the moment of inclusion, the patients starts reporting in de DizzyQuest App. This is a daily questionnaire of 31 questions addressing general functioning. In case of an attack, a short questionnaire is to be filled out. The inclusion and exclusion criteria will be double-checked by the coordinating investigator and if the patient does meet the criteria, the first survey package is sent through email. This survey pack consists of the HADS, DHI, THI, SF-36, EQ-5D VAS, NPQ, VADL, VAP and a questionnaire about expectations of the treatment.

All the pre-operative data is entered in Castor.

 The VAP and VADL are newly developed questionnaires to assess the effect of dizziness and/or balance problems on patients' ability to do things. They are not an outcome measure in this study, but we aim to anticipate on the possibility that the Bárány Society takes the outcomes of questionnaires into account in future studies. These questionnaires are taken for this trial as well, to enable comparison of the results of this study in the future that only use the VAP and the VADL.

In the following weeks, the patient visits the vestibular therapist, who takes the medical history and performs the first measurements. The patient is seen by the anaesthetist for regular pre-operative screening.

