### 10.1 Primary study parameter

The primary outcome is defined as being attack free at 12 months follow-up. The required significance level of findings ( $\alpha$ ) will be equal to or lower than 5%. Any statistical tests will be two-sided. P-values will be presented. Where confidence limits can be estimated, the confidence level will be 95%. All analyses will be performed by intention to treat.

A chi-square test (or Fisher's exact test) will be performed on the primary outcome variable data (number of patients free of vertigo attacks at 12 months post-operatively, in EDB vs endolymphatic sac decompression group).

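### The secondary mixed model (10.2.2) is specified by arm and visit with no stated baseline term or constraint, so as written it is valid but less precise than the collected data allow

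*Protocol*

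**What the plan says.** Protocol 10.2.2 is the whole model specification for the secondary outcomes: "All secondary outcomes will be analysed using a linear mixed model (EDB vs decompression group) at the different time measurement point". No covariate is named. Nothing is said about whether time 0 is a response, or whether baseline means are constrained. Section 10.2 adds only descriptive summaries, and 10.2.1 only missing questionnaire items. The one other general statement on method, in 12.6.1, plans non-parametric tests and refers to the Mann-Whitney test, which is also an unadjusted two-group comparison.

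The baseline data are listed in 8.3.1. On the questionnaires: "This survey pack consists of the HADS, DHI, THI, SF-36, EQ-5D VAS". On attack frequency, one of the recorded items is "Mean number of attacks per month in the last 6 months". Pure tone and speech audiometry is also done before surgery. Section 8.1.2 defines the DHI and THI change categories against baseline and uses EQ-5D at 0, 3, 6 and 12 months. Baseline is therefore treated as a reference elsewhere, but 10.2.2 does not say how the model uses it.

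**The concern.** The secondary outcomes carry the trial's conclusions on quality of life, hearing, tinnitus and cumulative attacks. The trial was sized only for the primary proportion, "with anticipated 25% percent difference", with 32 evaluable patients per arm. At that size, a baseline measure that predicts follow-up is the cheapest source of precision available, and the stated model does not claim it.

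The sentence in 10.2.2 also fits several estimators: a post-operative comparison by arm, an unconstrained group-by-visit model including time 0, a change contrast, or a constrained baseline model. They differ in precision. Leaving the choice open allows it to be made after the data are seen.

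**Working it through.** **The plan's own figure.** The protocol gives no SD, target effect, correlation or power for any secondary outcome, so there is no secondary figure to reproduce. Its only sample size, 32 per arm in 4.4, is for the primary endpoint with Fisher's exact test at 95% vs 70%. Exact enumeration does not reproduce that figure: two-sided power is 68.0% at 32 per arm, and 80% is first reached at 39 (80.7%). That is a separate matter. Here 32 serves only as the number evaluable per arm.

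**Inputs from the protocol.** n = 32 per arm, 1:1 (4.4); alpha 5% (4.4 and 10.1); "Any statistical tests will be two-sided" (10.1).

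**Assumptions.** rho = 0.2 to 0.7; equal SD at baseline and follow-up; one post-operative visit; 80% power for the unadjusted comparison.

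**Step 1: the effect that gives 80% unadjusted power.**

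d = (1.960 + 0.842) × √(2/32) = 2.802 × 0.25 = 0.70 SD.

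**Step 2: variance per patient, in units of the outcome variance.**

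- Follow-up value only: 1. With complete data, an unconstrained group-by-visit model with time 0 as a visit gives the same 12-month contrast, the raw difference.
- Change from baseline: 2(1 − rho), which exceeds 1 whenever rho < 0.5.
- Baseline as covariate: 1 − rho². Time 0 as a response with equal baseline means gives about the same.

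**Step 3: power.** Power = Φ(2.802/√v − 1.960), where v is the variance from step 2. At rho = 0.5 with the covariate, v = 0.75 and 2.802/0.866 = 3.235, so Φ(1.275) = 89.9%.

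| rho | Follow-up only | Change | Baseline-adjusted | Gain over follow-up only | 32 × (1 − rho²) |
|---|---|---|---|---|---|
| 0.2 | 80.0% | 60.1% | 81.6% | 1.6 | 30.7 |
| 0.3 | 80.0% | 65.8% | 83.6% | 3.6 | 29.1 |
| 0.4 | 80.0% | 72.5% | 86.4% | 6.4 | 26.9 |
| 0.5 | 80.0% | 80.0% | 89.9% | 9.9 | 24.0 |
| 0.6 | 80.0% | 87.9% | 93.8% | 13.8 | 20.5 |
| 0.7 | 80.0% | 95.1% | 97.5% | 17.5 | 16.3 |

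The last column is the number per arm at which an adjusted comparison matches the precision of 32 per arm unadjusted. A t-based calculation agrees to about 0.1 point.

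**Step 4: sensitivity to the starting power.** At rho = 0.5 the gain is 11.9 points from 50% unadjusted power, 11.8 from 70%, 9.9 from 80%, 6.3 from 90% and 3.6 from 95%.

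**Step 5: average over three visits.** With all correlations equal to 0.5, the variance of the three-visit mean is (1 + 2 × 0.5)/3 = 0.667 unadjusted and 0.667 − 0.25 = 0.417 adjusted. Power of 80.0% becomes 94.3%, a gain of 14.3 points.

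**The case against.** The strongest reply is that silence is not exclusion. Section 10.2.2 is one sentence, does not limit the measurement times to post-operative visits, and does not say that baseline is left out. With EQ-5D used from time 0 and change categories defined against baseline, the authors may intend time 0 to be in the model. With baseline means constrained equal, that model is as precise as covariate adjustment. Covariate lists are also often left to the statistical analysis plan, which is not shown.

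Much of this stands. A reader might infer that the plan rules baseline out; the text does not support that. But inclusion of time 0 is not enough: the precision comes from the constraint or the covariate, and the protocol states neither. Nor does it defer the model to another document.

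A second reply is that randomisation keeps the unadjusted contrast unbiased and that its confidence interval already reflects chance imbalance. That stands in full. A reader might infer from the small arms, and from stratification on gender and disease duration only, that the secondary estimates would be biased. They would not; the issue is efficiency.

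A third reply is that no power loss can be read from the documents. This also stands: the correlation and the unadjusted power are both assumed, and the main table is for a single visit rather than the full mixed model.

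**Conclusion.** The point holds as one of efficiency and pre-specification, of minor weight. The stated comparison is valid, and nothing in it is an error. It is less precise than the collected data allow under each reading that lacks a baseline covariate or constraint, provided baseline and follow-up are correlated.

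The size is a range: about 2 to 18 points of power for rho 0.2 to 0.7, at 32 per arm, two-sided 5% and 80% unadjusted power. A single figure such as 10 points is tempting, but it needs rho near 0.5 and that starting power, and the protocol gives neither. The gain will differ by outcome and is small where rho is low or the unadjusted power is already high.

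**What to change.** Add to 10.2.2: for each continuous secondary outcome with a baseline measurement, the mixed model includes the baseline value of that outcome and its interaction with visit as covariates; or, equivalently for this purpose, time 0 enters as a response with baseline means constrained equal across arms. Name one of the two. For the cumulative incidence of vertigo bouts, include the pre-operative attack rate recorded under 8.3.1 as a covariate.

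No new data are needed for DHI, THI, SF-36, EQ-5D VAS, audiometry or attack rate. FLS is not in the pre-operative pack listed in 8.3.1, although 8.1.2 compares it with baseline, so its baseline collection should be confirmed before the same rule is applied to it.

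With three post-operative visits (3, 6 and 12 months), the covariate form costs three parameters per model with the visit interaction, or one without it.
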